# Dual-task training with progression from variable- to fixed-priority instructions versus dual-task training with variable-priority on gait speed in community-dwelling older adults: A protocol for a randomized controlled trial

**DOI:** 10.1186/s12877-020-1479-2

**Published:** 2020-02-22

**Keywords:** Falls, Older adults, Dual task, Balance training, Functional activities

## Abstract

**Background:**

Functional independence and safe mobility, especially in older people, mostly rely on the ability to perform dual tasks, particularly during activities with variable- and fixed-priority attention. The aim of this study is to compare the dual-task training with progression from variable- to fixed-priority instructions versus dual-task training with variable-priority on gait speed in community-dwelling older adults.

**Methods:**

This is an assessor- and participant-blinded, two-arm, randomized controlled trial with 60 community-dwelling male and female older adults between the ages of 60 and 80 years old. Participants will be randomly allocated into either the intervention group or the control group using a computer-generated permuted block randomization schedule. The intervention group will undertake a progressive dual-task training in which the participants will be progressively submitted to dual-task walking and postural balance exercises with variable- to fixed-priority instructions. The control group will be submitted to dual-task training with variable-priority attention exercises. Both groups will receive 48 sessions lasting for 60 min each over 24 weeks. The primary outcome will be the gait speed under single- and dual-task conditions. Secondary outcomes will include spatiotemporal gait parameters, functional balance, executive function, falls, quality of life, and depression symptoms. All the analyses will be based on the intention-to-treat principle.

**Discussion:**

This is the first assessor- and participant-blinded, two-arm, randomized controlled trial with 6 months of intervention and an additional 6-month post-training follow up aiming to evaluate the effectiveness of training with progression from variable- to fixed-priority instructions on gait biomechanics, postural balance, falls episodes, executive functioning, and quality of life in community-dwelling older adults. If our hypotheses are confirmed, this training protocol can be implemented widely to improve gait speed and other functional activities and quality of life in community-dwelling older adults. This study protocol can be used to improve these functional aspects of community-dwelling older adults. This study may also contribute to future guidelines for the improvement of these clinical and biomechanical aspects in older people.

**Trial registration:**

ClinicalTrials.gov Identifier - NCT03886805, Registered 22 March 2019.

## Background

Older adults have an increased risk of falling, especially when they are required to perform a concurrent cognitive or secondary motor task while walking and carrying objects or paying attention to traffic [1–3]. In community-dwelling older adults this type of dual-task activity also significantly reduces gait speed [4] and increases gait variability [5–9]. Dual-task activities can be performed by shifting attention between tasks (dual task with variable-priority instructions) or placing equal amounts of attention on both tasks (dual task fixed-priority instructions) [10].

Regarding dual-task instruction priority, the literature has shown a bit more effect of training under variable- than fixed-priority instructions, although both are considered to have a great effect size [11]. These results are likely why participants trained under variable-priority instruction are able to learn faster and retain instruction better than dual-task training with fixed-priority instruction [12]. Nevertheless, we must consider that motor and cognitive tasks are often and simultaneously demanded in everyday situations, and so these tasks should be trained in protocols aiming for a dynamic postural balance in older adults. In addition, we can assume that fixed-priority instructions could be adopted as a progression of the variable-priority method since the learning and retention of the simultaneous motor and cognitive tasks of the former method appear more complex than the latter. Based on this rationale, in the first 12 weeks of training, both groups will be trained with dual-task activities exclusively under variable-priority instructions so that they can better learn and retain the motor and cognitive gains provided by this type of dual-task training, as already shown in the literature [12]. Over the next 12 weeks, only the participants in the control group will continue to evolve into the dual-priority variable task training. The experimental group will receive an exclusively dual-task training with fixed-priority, to better mimic most of the functional activities of daily living. To our knowledge, no research to date has attempted to prove this rationale.

In addition, although short-term benefits of dual-task exercises are known, the required frequency, duration, and intensity of training programs and need for supervision are still inconclusive [13], especially on static and dynamic postural stability [11]. Furthermore, there is low methodological quality among the existing studies regarding short-term follow ups [14].

Therefore, this protocol for a 6-month controlled trial with a 6-month follow up post-training will examine whether a dual-task protocol training with progression from variable- to fixed-priority instructions is more effective than only variable-priority dual-task protocol training for improving gait speed in community-dwelling older adults. We hypothesize that the experimental group’s (EG) participants who receive the proposed protocol (dual tasks with variable- and fixed-priority instructions) will achieve better improvements regarding the studied outcomes in comparison to the control group (CG) undertaking just dual tasks with variable-priority training.

## Methods/design

### Study design

This is an assessor- and participant-blinded, two-arm, randomized controlled superiority trial. The study has been written according to the recommendations of the World Health Organization, the International Committee of Medical Journal Editors, the Consolidated Standards of Reporting Trials (CONSORT) [15], and the Standard Protocol Items (SPIRIT) statements [16, 17]. This trial was prospectively registered at ClinicalTrials.gov (NCT03886805).

Sixty community-dwelling older adults between the ages of 60 and 80 years old will be randomly assigned to either dual-task training with activities progression from variable- to fixed-priority attention (EG) or to dual-task training with variable-priority attention (CG) for 6 months. The assessments will be performed at baseline (T1), at 3 months of intervention (T2), at the end of the 6 months of intervention (T3), as well as at 3 (T4) and 6 (T5) months post-intervention (Fig. 1). The T2 assessment was established in order to verify any change after the period when the EG will be trained only with fixed-priority instructions and the CG will be keeping trained with variable priority instructions.

**Fig. 1 Fig1:**
[figure not shown]
Flowchart of the study

### Study settings

The study data collection will be carried out in the Laboratory of Human Biomechanics and Functional Activity of the Department of Physical Therapy at the University of Pernambuco *Campus* Petrolina, Brazil. The protocol training will be carried out in the multi-sport gym of the Department of Physical Education, at the Federal University of Sao Francisco Valley, Brazil.

### Ethics approval, consent to participate and dissemination

This trial was approved by the Ethics Committee of the University of Pernambuco (CAAE: 71192017.0.0000.5207). All patients will be asked to provide written informed consent prior to randomization, using standard forms.

### Sample size

Gait speed (primary outcome) under fixed-priority dual tasks was used to calculate the sample size [18]. We adopted a minimal clinically important difference of 0.05 m/s, an effect size of 0.20 [19], a power of 95% (1 - β), an alpha of 0.05, and a design of *F*-statistic repeated measures with a within- and between-subjects interaction effect. Forty-eight participants were initially obtained as the study sample total. Taking into account a 20% sample loss, 60 participants will be assessed and allocated to the study by a ratio of 1:1. The sample size was calculated using the G*Power 3 [20].

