Note: *CG* Control group (dual-task training with variable priority attention), *EG* Experimental group (dual-task training with progression of activities from variable to fixed priority attention); ^a^Secondary cognitive or motor task will always be interspersed with dual tasks with variable priorities; ^b^Secondary cognitive or motor task will always be performed simultaneously with dual tasks with fixed priorities

Participants of both groups must attend at least 75% [26] of the 60-min training sessions, which will occur twice a week for 24 weeks. Each of the 48 group training sessions (maximum of 15 participants in each group) will include: i) a warm-up (10 min) with supervised walking on a flat surface and static postural balance exercises, ii) training (four stations, 10 min each, total of 40 min) for protocol execution, and iii) a cool-down, including breathing exercises and global muscle stretching (10 min). The principles of this training will follow recommendations from previous studies [26–29]. Interventions of each group will be supervised by a physical therapist with experience in ​​dual-task exercises and by four undergraduate students of the final year’s physical therapy course. Adherence monitoring will be done by signature in the presence table in each training session. Concomitant exercise programs for postural balance are not permitted during the trial for both groups.

The dual-task training program is designed based on activities described by Wollesen et al. [29] as well as the studies by Strouwen et al. [30] and Zhao and Pak-Kwongchung [31]. Table 1 presents the conceptual basis that will be used to structure the dual-task protocol training. The progression of the protocol will be based on eight foci (F1–F8), while strategies will progress in intensity and degree of difficulty; the tasks will be determined by associating the respective foci (F1–F8) with the strategies. This will allow for the graduation of the challenge level at each training stage regarding participants’ postural control and gait pattern.

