### Statistical analyses

Statistical analyses will be performed based on the intention-to-treat principle. The independent variables of the clinical trial will be both groups (two levels) and the time, counted in weeks (five levels; T1 to T5).

The pattern of missing data will be previously analyzed [55]. A full description of the reasons for possible sample losses will be presented after the end of the study. Exploratory analyses will be performed to verify the distribution of variables, identification of outliers, missing data, and asymmetries.

Generalized Estimation Equations (EEG) will be used for univariate analyses, considering the factors group (EG and CG) and time (T1, T2, T3, T4 and T5), as well as the interaction effect (time vs. group). The most appropriate GEE model for each variable will be confirmed by considering the measurement scale, the Quasi-likelihood Information Criterion (QIC) values, the working correlation matrix, the data distribution, and the respective log link.

Adjustments for univariate (main effects) and multivariate (interaction effect) comparisons of estimated marginal means (EMM) will be made by the Sidak test.

A 95% confidence interval for the mean difference that lies entirely on the EG side will be considered a superiority result statistically significant.

The Statistical Package for the Social Sciences (SPSS, IBM; v.22.0) will be used for statistical analyses.

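### The 95% power belongs to an interaction F-test at Cohen's f = 0.20; it is not tied to the 0.05 m/s MCID or to the confidence-interval rule that decides superiority

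*Protocol article*

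**What the plan says.** The Sample size section names the endpoint: "Gait speed (primary outcome) under fixed-priority dual tasks was used to calculate the sample size [18"]. It then sets three figures side by side: "We adopted a minimal clinically important difference of 0.05 m/s, an effect size of 0.20 [19], a power of 95" per cent. Alpha is 0.05, and the design is a repeated-measures F-test of the within-between interaction, run in G*Power 3. The result is reported as: "Forty-eight participants were initially obtained as the study sample total". A 20% loss takes this to 60, allocated 1:1. The section gives no SD and no within-person correlation, and does not say what kind of effect size 0.20 is.

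The Statistical analyses section plans a GEE with group, time (five levels, T1 to T5) and their interaction, with Sidak adjustment of comparisons between estimated marginal means. Superiority is declared on a different quantity: "A 95% confidence interval for the mean difference that lies entirely on the EG side". No visit is named for that interval.

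The Background and Intervention sections give both arms the same variable-priority training until T2. They differ only from then on.

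**The concern.** Placed next to each other, the three figures read as 95% power to detect 0.05 m/s. That holds only if 0.05 m/s and 0.20 describe the same effect and the powered test is the one that decides the trial. The text shows neither.

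The effect size in the G*Power interaction module is Cohen's f, a ratio of the spread of the interaction means to the SD. It is not a difference divided by the SD. For two groups over five visits, a given f corresponds to a much larger standardised group difference than its numerical value suggests. In addition, an omnibus test on 4 degrees of freedom and a confidence interval for one mean difference do not share the same power. What is at stake is how the stated power, and with it a non-significant result, can be interpreted against the trial's own MCID.

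**Working it through.** **1. Reproducing 48.** Inputs from the protocol: f = 0.20, two groups, m = 5 visits, alpha 0.05. Assumed: r = 0.5, sphericity 1.

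λ = f²·N·m/(1 − r), df1 = m − 1, df2 = (N − 2)(m − 1).

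For N = 48: λ = 0.04 × 48 × 5/0.5 = 19.2, df 4 and 184, power 0.952. For N = 46, power is 0.942. So N = 48, and 48/0.8 = 60. The stated figures reproduce. This set of inputs is the most plausible but not unique: four, three or two measurements with r of about 0.57, 0.64 or 0.72 also give 48. In no case is 0.05 m/s an input.

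**2. What f = 0.20 means here.** With group differences d_t over the visits, the interaction cell effects are ±(d_t − mean d)/2, and f is their root mean square divided by the SD.

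- Difference D at T3, T4 and T5: mean 0.6D; mean squared deviation (2 × 0.36 + 3 × 0.16)/5 = 0.24 D²; f = √(0.24/4)·D/SD = 0.245 D/SD. Then f = 0.20 gives D = 0.82 SD.
- Difference D at T3 only: mean 0.2D; mean squared deviation (4 × 0.04 + 0.64)/5 = 0.16 D²; f = 0.20 D/SD. Then D = 1.0 SD.

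For D = 0.05 m/s the SD must be 0.05/0.82 = 0.061 or 0.05/1.0 = 0.050 m/s.

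**3. The other reading.** If 0.20 was meant as 0.05/SD, the SD is 0.25 m/s and f = 0.245 × 0.20 = 0.049. Omnibus power with N = 48 is then 11% at r = 0.5, and 44% even at r = 0.9.

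**4. The decision rule at the protocol's own f = 0.20.** Take 24 per arm and a two-sided 95% interval at one visit: noncentral t, 46 df, δ = (D/SD)·√(24/2), divided by √(1 − r²) if baseline-adjusted.

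- D = 0.82 SD: δ = 2.83, power 79%. Baseline-adjusted at r = 0.5: δ = 2.83/0.866 = 3.27, power 89%. With a Sidak correction over five visits (an assumed family; alpha 1 − 0.95^(1/5) = 0.0102), unadjusted power is 56%.
- D = 1.0 SD (T3 only): 92% unadjusted, 97% baseline-adjusted, 78% unadjusted with the same Sidak correction.

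**5. Power for 0.05 m/s held over T3 to T5, N = 48.** The SD and r are assumed.

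| SD (m/s) | Omnibus r = 0.5 | r = 0.7 | r = 0.8 | r = 0.9 | One-visit CI, unadjusted | Adjusted, r = 0.5 | Adjusted, r = 0.8 |
|---|---|---|---|---|---|---|---|
| 0.10 | 54% | 79% | 94% | >99% | 40% | 50% | 81% |
| 0.15 | 25% | 41% | 59% | 90% | 20% | 26% | 47% |
| 0.20 | 16% | 24% | 35% | 65% | 13% | 16% | 29% |
| 0.25 | 11% | 16% | 23% | 44% | 10% | 12% | 20% |

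**The case against.** The best defence is that the protocol gives neither SD nor correlation, so inadequate power cannot be shown. That stands. At SD 0.10 the omnibus test reaches 94% with r = 0.8, and entry is limited to people with a Berg score of at least 52 who walk at 1 m/s or faster, which could narrow the SD. The cited sources behind 0.05 m/s and 0.20 are not available here and may explain the link. An article may also leave such detail to a fuller document. What remains is that the printed figures agree only under a narrow condition that the text neither states nor supports.

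It is also fair that the planned GEE contains the group-by-time interaction, so the powered hypothesis is part of the analysis. The interval rule names no visit, so reading it as a single-visit comparison is one interpretation. A one-degree-of-freedom contrast of T3–T5 against T1–T2 would have about 99% power or more at an SD of 0.05 to 0.061 m/s. But the plan does not name that contrast, and the rule that declares superiority is not the omnibus test.

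A higher correlation helps the true power but does not explain the printed calculation: with f = 0.20 and five visits, r = 0.7 or 0.8 would have given 30 or 20 participants, not 48.

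Two stronger inferences are not supported. A reader might conclude that the trial lacks 95% power for 0.05 m/s; without the SD and r, that is unproven. A reader might also fear that a null result will be taken to exclude a 0.05 m/s benefit; the protocol defines only a superiority reading and says nothing of the kind.

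**Conclusion.** The concern holds in a limited form. The sample size is arithmetically correct for an omnibus interaction test at f = 0.20, but the MCID plays no part in it. At r = 0.5, 95% power for 0.05 m/s requires an SD of about 0.05 to 0.06 m/s; on the reading 0.20 = 0.05/SD, power is about 11%. Between these, the answer depends on two quantities that are not given: at SD 0.10, omnibus power is 54% at r = 0.5 and 94% at r = 0.8; at SD 0.15, 25% and 59%. The claim is therefore unsupported rather than disproved.

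The mismatch with the decision rule needs no assumed SD in m/s. At f = 0.20 with the difference held over T3 to T5 and 24 per arm, a single-visit interval has 79% power unadjusted or 89% baseline-adjusted (r = 0.5), and less with Sidak adjustment. It is milder (92% unadjusted) if the effect is confined to T3. These figures rest on no group difference up to T2 and on a single-visit reading of the interval.

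**What to change.** Keep 60 participants and rewrite the Sample size paragraph:

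- Name the contrast and visit to which the superiority interval applies, here and in Statistical analyses.
- State that 0.20 is Cohen's f if that is what was entered, and give the SD of dual-task gait speed with its source, the within-person correlation and the number of measurements used.
- Replace the 95% power placed beside 0.05 m/s with the power, or the detectable difference, for the named contrast over a range of correlations. For example, for a baseline-adjusted single-visit comparison with 24 per arm and two-sided 5%, the detectable difference at 80/90/95% power is 0.72/0.83/0.92 SD at r = 0.5, and 0.50/0.57/0.64 SD at r = 0.8 (the unadjusted 0.83/0.96/1.06 SD times √(1 − r²)). Baseline adjustment is an illustration; if the sponsor chooses it, the analysis section must say so.

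The cost is text only, with no added participants. The drawback is that the stated power will probably look less favourable than 95%.

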### Participants and recruitment

Participants will be recruited from community health centers and other settings that have specialized health care for older people, such as parks, squares, and churches in the city. Announcements on radios, local newspapers, and social networks (Facebook and Instagram) will be used. All participants will sign a consent form before starting the assessments.

### Eligibility criteria

Participants of both sexes between the ages of 60 and 80 years will be included in this study. For security reasons, only individuals presenting a score of ≥52 (up to a maximum of 56) on the Berg Balance Scale [18], a score of ≥24 (up to a maximum of 30) on the Mini-Mental State Examination [21], and who are able to walk uninterrupted for a distance of 10 m at a self-selected velocity of at least 1 m/s without assistance from another person, cane, or walker will be included. Potential participants will be excluded if they (i) have any contraindication to postural balance and cognitive exercise, (ii) have fallen two or more times in the last 12 months, (iii) participate or have participated in any regular or structured physical exercise program two or more times per week in the last 6 months, (iv) have a chronic health condition for which exercise is contraindicated, (v) have had any upper or lower limb fracture in the last 6 months [22], (vi) have evidence of any surgical procedures to the knees, ankles, or hips or have had muscle damage in the last 6 months [23], (vii) have self-reported uncontrolled diabetes, (viii) no able to speak and understand the Portuguese language, and (ix) refusal to give informed consent.

### Concealed allocation

The concealed randomization system schedule will be prepared by an independent researcher ([name]) who is not aware of the numeric codes for the EG and CG. The numerical sequence will be maintained in opaque envelopes sequentially numbered from 1 to 60, following the order generated by the software. The randomization procedure will follow the instructions described in the literature [24]. The code sequence will be kept confidential and stored in a location that blind assessors, participants, and the statistician of this clinical trial will not have access to until the end of the study.

### Blinding

Participants, assessors and the statistician will be blinded regarding the group allocation. All assessments of the study outcomes will be conducted by assessors blinded to group allocation. Considering that both groups will undergo variable-priority activities at some stages of the training protocol, participants will not have the ability to differentiate which group they are allocated to. Thus, we consider participants to be blind to allocation. On the other hand, due to the nature of the intervention, physical therapists cannot be blinded to allocation. However, they will be strongly encouraged to not disclose the allocation status of the participants at the follow-up training [25].

Before each assessment, all participants will be instructed to not disclose what type of training they are receiving. Code breaks should occur only in exceptional circumstances when knowledge of the dual-task balance protocol training is essential for further management of the participant.

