### Intervention

The EG will be trained with variable-priority instruction activities during the first 3 months (T1 to T2) and in the subsequent 3 months (T2 to T3) will be submitted to training with fixed-priority instructions activities. The GC will be trained under variable-priority instruction activities over the 6 months (T1 to T3). The detailed evolution of each of the groups can be found in Tables 1 and 2.

**Table 1 Tab1:** Detailed conceptual basis regarding foci, tasks, and respective progressions to structure the training protocol

Focus	Strategy	Task
1. Postural balance	a) Change the base of support	**Standing** 1) Normal standing (bipodal support with feet separated at shoulder width 2) Feet together (bipodal support with feet side by side) 3) Semi-tandem stance 4) Tandem stance 5) One leg support on the dominant leg 6) One leg support on the non-dominant leg
		**Walking** 7) Semi-tandem 8) Tandem
	b) Displace the center of mass in different directions and with different bases of support	1) Sequentially perform F1a (1–6) by first laterally moving the trunk with shoulder abducted at least above 60 degrees 2) Sequentially perform F1a (1–6) by first laterally moving the trunk with the arms alongside the body
	c) Reach the body limits of stability and holding them at this point	1) Sequentially perform F1a (1–6) by first laterally moving the trunk with shoulder abducted at least above 60 degrees 2) Sequentially perform F1a (1–6) by first laterally moving the trunk with the arms alongside the body
	d) Change the somatosensation input (stability/complacency of the support surface)	Standing on different surfaces (rigid, soft or rough) 1) Sequentially perform F1a (1–6)
		Walking on different surfaces (rigid, soft or rough) 2) Sequentially perform F1a (7–8)
	e) Change the vision input	Standing with eyes closed 1) Sequentially perform F1a (1–6)
		Walking with eyes closed 2) Sequentially perform F1a (7–8)
2. Muscle strength and power, and postural balance during stationary activities performance	a) Standing still in a semi-squatting posture	1) Increase the time staying in this posture
	b) Weight-loaded in a single-leg stance	1) Gradually increase the standing time in this posture
	c) Sit to stand	1) Increase the number of cycles per seconds (starting at a frequency of one cycle per second)

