#### Secondary outcome measures

Gait variables, functional mobility and balance tests, reactions time, confidence and fear of falls, quality of life, depression symptoms and fall episodes are the secondary outcomes and will be assessed at all the time points. These secondary outcomes presented in Table 3 were chosen because they represent the functional, biomechanical, and quality of life aspects of patients at risk for falls.

**Table 3 Tab3:** Schedule of forms and procedures of the study

				−1	0	T1	T2	T3	T4	T5
Activity/ Assessment	CRF (Y/N)	Staff member	Approximate time to complete	Pre-study screening/ consent	Pre-study baseline/ randomization	Study visit 1 immediately post-randomization	Study/ interim visit 2 (3 months)	Study/ interim visit 3 (6 months)	Post-intervention follow-up (3 months)	Post-intervention follow-up (6 months)
Pre-screening consent	N	Study Coordinator	5 min	X						
Screening log	N	Study Coordinator	5 min	X						
Inclusion/ exclusion form	Y	Study Coordinator	N/A	X						
Demographic data	Y	Interviewer	10 min		X					
Anthropometric data	Y	Assessor	5 min		X					
Gait speed, general, temporal and spatial variables	N	Assessor	15 min			X	X	X	X	X
Displacement of the body center of mass during *quasi*-static posture	N	Assessor	15 min			X	X	X	X	X
Functional balance tests	Y	Assessor	15 min			X	X	X	X	X
Mobility test	Y	Assessor	10 min							
Reaction time	Y	Assessor	10 min			X	X	X	X	X
Confidence and fear of falls	Y	Interviewer	10 min			X	X	X	X	X
Quality of life	Y	Interviewer	10 min			X	X	X	X	X
Depression symptoms	Y	Interviewer	10 min			X	X	X	X	X
Fall episodes	Y	Interviewer				Monthly				
Adverse events	Y	Study Coordinator	*N/A*			As needed throughout the protocol				
Adherence to the exercise program	Y	Interviewer				Monthly				

*CRF* Case report form, *N/A* Not applicable

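### The reason given for not blinding therapists applies only from week 13; allocation could be kept from them during the 12 weeks when both arms train identically

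*Protocol article*

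**What the plan says.** All references are to the protocol article.

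- **Blinding.** Participants, assessors and the statistician are blinded. Therapists are not: "due to the nature of the intervention, physical therapists cannot be blinded to allocation". The only safeguard for them is that "they will be strongly encouraged to not disclose the allocation status of the participants at the follow-up training".
- **Concealed allocation.** The code is "stored in a location that blind assessors, participants, and the statistician of this clinical trial will not have access to" until the study ends. Therapists are not on that list, and no time is given at which they learn the allocation.
- **Background.** "in the first 12 weeks of training, both groups will be trained with dual-task activities exclusively under variable-priority instructions".
- **Intervention.** The experimental group (EG) has variable-priority training from T1 to T2 and "in the subsequent 3 months (T2 to T3) will be submitted to training with fixed-priority instructions activities". The control group (CG) stays on variable-priority training throughout. In Table 2, the EG entry for each of stages 1-4 (weeks 1-12) simply refers back to the CG entry.
- **Table 3.** T1 is labelled "Study visit 1 immediately post-randomization", so allocation exists before training begins.

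**The concern.** The nature of the intervention can prevent blinding only when the two interventions differ. For the first half of the programme they do not, so the delivering staff have no stated need to know the arm.

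Knowledge of the arm could matter because delivery leaves room for discretion on something close to the primary outcome, dual-task gait speed. Table 1 (focus 3, strategy a) has participants raise their walking speed step by step, with no set pace, and Table 2 schedules this from stage 1. The text after Table 2 has instructors explain the exercises and give spoken feedback. The investigators hypothesise that the EG will do better, so the direction of any expectation is foreseeable. A real difference in coaching would be measured accurately by a blinded assessor and would appear as a difference between arms before the planned contrast has begun.

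**Working it through.** **1. Programme length.** The Intervention section gives sessions "which will occur twice a week for 24 weeks": 24 weeks × 2 = 48 sessions, which matches the stated 48.

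**2. Common phase.** Table 2 stages 1-4 cover weeks 1-3, 4-6, 7-9 and 10-12. 12 weeks × 2 = 24 sessions, and 24/48 = 50%.

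**3. Does the stated reason hold in each half?**

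| Weeks | EG content | CG content | Must therapists know the arm to deliver it? |
|---|---|---|---|
| 1-12 | variable-priority, same tasks as CG | variable-priority | No |
| 13-24 | fixed-priority | variable-priority | Yes |

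The reason is sound for the second row and fails for the first. The Blinding section does not separate them.

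**4. Who could know, and when.** Randomisation precedes T1 (Table 3), so the allocation exists at least 12 weeks before it is needed. The article neither withholds it from therapists nor says when they receive it. Awareness from session 1 is therefore allowed, but not stated.

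**5. Can a size be attached?**

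- *Early loss.* The Sample size section allows 20% of 60 = 12 losses, with nothing on timing or split by arm. The number lost before week 13 can be anything from 0 to 12. For example, losses spread evenly over 12 months give 12 × 3/12 = 3. No difference between arms can be computed.
- *Coaching effect.* The article gives no figure from which a gait-speed difference due to coaching could be derived. Dividing an assumed value by the stated 0.05 m/s would only restate the assumption.

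**6. Effect on sample size.** None. The planned 48/(1 − 0.20) = 60 does not depend on when therapists learn the allocation.

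**7. A conflict in the premise.** The Study design section describes T2 as checking change after a period in which the EG has had only fixed-priority training. The Background, the Intervention section and Table 2 put fixed-priority training after T2. This point rests on those three places; the passages must be reconciled.

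**The case against.** The strongest reply is that the design already watches for the problem. T2 falls at the end of the common phase, gait speed is measured then by blinded assessors, and the Statistical analyses section models group, five time levels and their interaction. A difference built up by week 12 would appear in the T2 contrast, and change from T2 to T3 can be compared between arms. This stands. A reader might infer that early therapist influence could never be separated from the effect of progression; the plan does not support that.

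Two limits remain. T2 shows only those still in the trial, and the estimate would be imprecise. As an illustration, take 24 per arm, an unadjusted comparison and an assumed SD of 0.125 m/s (0.05/0.4, reading the stated effect size 0.20 as Cohen's f, so d = 0.4). The 95% interval is then about ±1.96 × 0.125 × √(2/24) = ±0.07 m/s. With an SD of 0.25 (0.05/0.20, reading it as d) it is about ±0.14 m/s.

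Other parts of the reply also stand:

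- **Exposure is inferred.** A reader might take the unqualified sentence to mean that therapists know the arm from session 1. The article does not say so. Therapists could not be on a list of people denied the code until the end of the study, because they must deliver different content from week 13.
- **Early dropout that depends on arm is not shown.** Participants are described as blind and receive identical content, so the arm could act only through therapist behaviour or disclosure.
- **Task progression is fixed by calendar week and is the same in both arms.** That leaves encouragement, feedback and intensity within tasks as the open routes.
- **The second half is untouched.** Therapists cannot be blinded in weeks 13-24, and the article says openly that they are not.

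None of this supplies a reason for therapists to know the arm in weeks 1-12.

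**Conclusion.** The point holds as a cheap improvement. The reason given for leaving therapists unblinded does not apply to 24 of 48 sessions, and the protocol neither withholds the allocation from them in that period nor says when they receive it. The risk is one of differential coaching or encouragement during a phase meant to be identical. Assessor blinding does not remove it, and T2 makes it visible only in part.

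The conclusion assumes that weeks 1-12 run as the Background, the Intervention section and Table 2 describe. It does not claim that bias will occur, that early losses will differ by arm, or that any particular gait-speed difference is expected. The document supports none of these.

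**What to change.** Amend the Concealed allocation and Blinding sections so that:

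1. Randomisation assigns participants to coded classes. With at most 15 per class, 60 participants need at least 60/15 = 4 classes, or two per arm.
2. The independent code holder tells the therapists, and the students who help supervise sessions, what each code means only at the start of week 13.
3. T2 assessments are scheduled before that date where the 7-day margin on either side allows. Release should be tied to the start of week 13, not to the last T2 assessment, so that one late visit does not hold up training.
4. The text says that therapists are blinded in weeks 1-12 and unblinded in weeks 13-24.

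In the same amendment, reconcile the description of T2 under Study design with the Background, the Intervention section and Table 2.

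**Cost.** A wording change, with the code holder keeping the meaning of the codes for 12 more weeks. No extra participants or staff are needed. Instructors would be briefed on the arm-specific programme at week 12 instead of at the start. The change does not remove class or instructor differences between arms, so it does not guarantee that early loss is unrelated to arm. It removes only the part that comes from therapists knowing the allocation.
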